## Abstract

**Background:**

In manufacturing industries, tasks requiring poor posture, high repetition, and long duration commonly induce fatigue and lead to an increased risk of work-related musculoskeletal disorders. Smart devices assessing biomechanics and providing feedback to the worker for correction may be a successful way to increase postural awareness, reducing fatigue, and work-related musculoskeletal disorders. However, evidence in industrial settings is lacking.

**Objective:**

This study protocol aims to explore the efficacy of a set of smart devices to detect malposture and increase postural awareness, reducing fatigue, and musculoskeletal disorders.

**Methods:**

A longitudinal single-subject experimental design following the ABAB sequence will be developed in a manufacturing industry real context with 5 workers. A repetitive task of screw tightening of 5 screws in a standing position into a piece placed horizontally was selected. Workers will be assessed in 4 moments per shift (10 minutes after the beginning of the shift, 10 minutes before and after the break, and 10 minutes before the end of the shift) in 5 nonconsecutive days. The primary outcomes are fatigue, assessed by electromyography, and musculoskeletal symptoms assessed by the Nordic Musculoskeletal Questionnaire. Secondary outcomes include perceived effort (Borg perceived exertion scale); range of motion of the main joints in the upper body, speed, acceleration, and deceleration assessed by motion analysis; risk stratification of range of motion; and cycle duration in minutes. Structured visual analysis techniques will be conducted to observe the effects of the intervention. Results for each variable of interest will be compared among the different time points of the work shift and longitudinally considering each assessment day as a time point.

**Results:**

Enrollment for the study will start in April 2023. Results are expected to be available still in the first semester of 2023. It is expected that the use of the smart system will reduce malposture, fatigue, and consequently, work-related musculoskeletal pain and disorders.

**Conclusions:**

This proposed study will explore a strategy to increase postural awareness in industrial manufacturing workers who do repetitive tasks, using smart wearables that provide real-time feedback about biomechanics. Results would showcase a novel approach for improving self-awareness of risk for work-related musculoskeletal disorders for these workers providing an evidence base support for the use of such devices.

**International Registered Report Identifier (IRRID):**

PRR1-10.2196/43637

## Introduction

The agenda for decent work, initially promoted by the World Labor Organization, and recently connected to the sustainable development goals of the United Nations [1], includes safety and security at work as one of its strategic axis [2]. The quest to fulfill this axis also reflects the increased demand from consumers regarding concerns about the development of fair and sustainable products. In the same line of concerns, some companies issue bonds incorporating the fulfillment of objectives related to the reduction of accidents at work [3]. Thus, the opportunities offered by the technological developments of the so-called Industry 4.0 could positively influence the indicators related to this set of objectives and concerns, namely with regard to musculoskeletal injuries. Musculoskeletal disorders (MSDs) are the most prevalent work-related health issues and one of the most critical public health problems worldwide [4,5]. Work-related musculoskeletal disorders (WMSDs) are mainly caused by the execution of work tasks and the environment in which work is performed [4]. In the manufacturing industries, tasks requiring excessive force, poor posture, high repetition, and long duration, which induce fatigue and which are stressful, lead to an increased risk of MSDs [4,6,7]. The consequences of WMSDs have a significant and wide-ranging financial impact on both the social and individual levels [8]. In Europe, about 3 of every 5 workers report MSDs. In assembly and manufacturing workers, the most common types of MSDs reported are back pain (55%) and muscular pain in the neck, shoulder, and upper limbs (47%), followed by the lower limbs (33%) [4]. MSDs are responsible for 15% of the total number of (disability-adjusted) life years. Furthermore, more than half (53%) of the workers with MSDs report work absenteeism. Therefore, a high burden on the economy and health care systems is not surprising. In addition, the individual, coworkers, and families are also affected, directly or indirectly, by the injured workers with an associated decrease in physical and mental health and quality of life [9,10].

Due to the high prevalence of musculoskeletal complaints and diseases, and the high associated burden, a significant effort has been made in the prevention of WMSDs [10]. Assessing exposure to risk factors of WMSDs is among the most successful strategies [11]. One of these emerging approaches is wearable devices [11-14]. These are rapidly developing, fostering the promotion of individual healthier lifestyles. Smart workwear is technology embedded into clothing that contacts the skin. This technology can monitor heart rate and movement delivering holistic information on fatigue and body stress. The real-time feedback of data provided can enhance the monitoring of health status, perhaps enabling earlier diagnosis or, in turn, hastening the integration of injury and illness prevention strategies [13,15]. Thus, comfortable smart workwear with movement and posture monitoring seems an adequate solution for the assessment of WMSDs risk and prevention of WMSDs. Although recent advances have been made in posture assessment and monitoring, few studies focus on compensatory adaptations that provide feedback to the user [16,17]. Injury prevention, due to inadequate posture or muscle fatigue, may be engaged with educational information and biofeedback delivered to the operator in real-time conditions or at strategically selected intervals of time during the work shift. Providing individual feedback to the worker may help decrease the exposure of individual workers to ergonomic risk factors and consequently, injury [18].

Thus, this study protocol aims to detect muscle fatigue related to repetitive activities and to explore a smart wear system for correcting biomechanics and reducing fatigue. The system involves the use of a wearable sensorized jacket and shoes and real-time feedback delivered to the worker. This system was created with the aim of preventing the unconscious development of awkward postures, compensatory movements, and fatigue, predisposing to injuries over time. The system will be tested through a single-subject experimental design with human subjects performing a repetitive task in real industry settings. The development of research in a real context on the factory floor raises different challenges. One of these challenges concerns the interference that investigation activities make in the normal production cycle. Thus, the methodological options should consider the least possible impact for the typical activities carried out there. In this sense, within the range of experimental work options, a single-subject experimental design will be able to contribute to these requirements.

## Methods

### Design and Setting

A longitudinal single-subject experimental design following the ABAB sequence [19] will be developed in a manufacturing industry real context. In the ABAB design, first, a baseline is determined (A), then the intervention is introduced, with the use of the smart wear and real-time feedback to the worker for the first time (B). Next, the intervention is withdrawn, returning to the baseline condition (A). Finally, after baseline stability is reestablished, the intervention is presented (B) for the second time [1,2]. All 4 periods will end with an assessment of the selected outcomes. Figure 1 depicts the study flow. Generally, in this study design, the research is done very thoroughly on 3 to 5 subjects. The interest is always in the meticulous examination of each participant individually, not in the group's average performance. Multiple single-subject experimental studies also present the opportunity to consider not only the individual variables but also analyze the trial at the environmental level [19,20].

**Figure 1 figure1:**
[figure not shown]
Study flow diagram. EMG: electromyography; NMQ: Nordic Musculoskeletal Questionnaire; RULA: Rapid Upper Limb Assessment.

### Ethics Approval and Consent to Participate

All participants will give informed consent to participate. All procedures are handled according to the Declaration of Helsinki and regulatory legislation, which includes approval by an ethics committee. The protocol is under review by the Ethics Committee of the University of Aveiro (17-CED/2023). Data will be processed complying with the European General Data Protection Regulation.

### Participants, Eligibility, and Recruitment

This study will include 5 active workers from an industrial manufacturing setting of household appliances in the Region of Aveiro, Portugal. To be included, workers must be aged between 35 and 45 years and have a work experience with the tested workstation for at least 6 months. Exclusion criteria are (1) history of vestibular disorders, (2) neurological, respiratory disease, or spinal surgery, (3) structural spinal problems, (4) medication or a health condition affecting balance, and (5) regular treatments for a musculoskeletal condition.

The workers will be recruited by the occupational health department, which will provide the identification numbers of each selected worker as well as shoe and clothing sizes.

### Study Procedure

A specific task representing a repetitive movement was chosen. The task consists of the vertical screw tightening of 5 screws in a standing position into a piece placed horizontally. A first assessment period will be executed to analyze baseline repetitive work (A) outcomes. Subsequently, the workers will use the smart wearables and be provided with real-time feedback for 4 weeks (B). A second assessment (assessment 2) will be performed to explore the efficacy of the system. Afterward, the workers will have a washout period of 4 weeks to reestablish baseline repetitive work condition (A), followed by assessment 3. Finally, a second 4-week period of intervention (B) and consequent assessment 4, will take place (Figure 1). Each assessment moment will be accomplished in 5 consecutive days, in 4 periods of the day, which includes measurements for each period of 5 cycles of the performed task in the first 10 minutes after starting the shift (to avoid the warm-up period), 10 minutes before the break time, 10 minutes after the break, and 10 minutes before the end of the day's shift. All tests will be performed guaranteeing that in the anterior 48-hour period each individual did not participate in strenuous physical activities, which may affect the selected outcomes.

### Smart Wearable Systems

The smart wearable systems consist of a sensorized jacket, smart footwear, a smart band, and a feedback system provided to the worker. The sensorized jacket aims to monitor the upper limb (shoulder flexion/extension and abduction/adduction and elbow flexion/extension) and trunk (lumbar flexion/extension) with strategically placed inertial measurement unit (IMU) systems and body temperature with a temperature sensor. Smart footwear consists of a shoe equipped with a set of 6 sensors Force Sensitive Resistors (Sensitronics), to map plantar pressures. The sensors have a 30-mm diameter and work in a 0-300–N force range. They were assembled in a custom substrate printed by RokuPrint (RP 2.2, RokuPrint GmbH). A smart band will monitor heart rate. The main system architecture is presented in Figure 2.

**Figure 2 figure2:**
[figure not shown]
Main system architecture. PPE: Personal Protective Equipment.

### Data Collection and Outcomes

The primary outcomes are fatigue and musculoskeletal symptoms. Fatigue will be assessed by electromyography (EMG) and musculoskeletal symptoms by the Nordic Musculoskeletal Questionnaire [21].

Secondary outcomes include perceived effort, assessed by the Borg Rating of Perceived Exertion (RPE), range of motion of the main joints in the upper body and trunk, speed, acceleration, and deceleration of movement, through motion analysis, risk stratification of range of motion of the upper limb and trunk based on limits defined in the Rapid Upper Limb Assessment (RULA) [22], and cycle duration in minutes.

For patient characterization, baseline questionnaires including sociodemographic data, physical activity level, quality of life, anxiety and depression, insomnia and sleep quality, fatigue, and pain and disability will be collected. Table 1 displays the assessment flow.

**Table 1 table1:** Assessment flow.

Measurements	Initial measurement	At the start of the shift	During the shift	After the end of the shift
Sociodemographic information and habits	✓			
Quality of life—EUROHIS-QOL-8	✓			
Musculoskeletal pain (NMQ^a^) and adapted NMQ	✓	✓		✓
Physical activity (RAPA^b^)	✓			
Anxiety (GAD-7^c^) and depression (PHQ-9^d^)	✓			
Subjective fatigue (FACIT-F^e^)	✓			
Sleep quality (BaSIQS^f^)	✓			
Heart rate			✓	
Joint range of motion			✓	
Ergonomic risk (RULA^g^)			✓	
Electromyography			✓	
Perceived exertion (RPE^h^)		✓	✓	✓

^a^NMQ: Nordic Musculoskeletal Questionnaire.

^b^RAPA: Rapid Assessment of Physical Activity questionnaire.

^c^GAD-7: General Anxiety Disorder 7-item scale

^d^PHQ-9: Patient Health Questionnaire-9.

^e^FACIT-F: Functional Assessment of Chronic Illness Therapy—Fatigue.

^f^BaSIQS: Basic scale on insomnia complaints and quality of sleep questionnaire.

^g^RULA: rapid upper limb assessment.

^h^RPE: rate of perceived exertion.

### Instruments

#### Electromyography

EMG recording will be conducted using the Cometa EMG wireless portable system (Covidien Kendall) with disposable silver 24-mm surface electrodes. Electrode application will proceed following the recommended procedures of skin preparation: shaving of the area; rubbing and cleaning with alcohol; following a 10-minute resting time to reduce skin impedance [23]. The EMG electrodes will be placed according to manufacturer’s recommendations on the upper trapezius, posterior deltoid, triceps medial, biceps brachii, the lumbar portion of the erector, biceps femoris, tibialis anterior, and gastrocnemius. All trials will be visually examined for signal quality and measurement errors. Muscle activity data will be collected with a sampling rate of 2000 Hz. EMG data will be processed with a customized MATLAB script (R2017b, MathWorks), where a fourth-order Butterworth band-pass filter from 10 to 500 Hz will be applied to minimize the appearance of electromyographic artifacts [24]. EMG signal will be normalized using a method that divides each point that constitutes the processed EMG by the peak value acquired from the same EMG. The root-mean-square of the EMG data and the averaged rectified value will be calculated to determine the signal amplitudes. Muscle fatigue will be characterized by median frequency and amplitude.

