### Data Analysis

Structured visual analysis techniques will be conducted to observe the effects of the intervention using a Single-Case Visual Analysis package for R. Graphical (RStudio) representations of data for each participant will be plotted considering primary and secondary outcomes on the y-axis and time on the x-axis. The results for each variable of interest will be compared in-between the different time points of the work shift and longitudinally considering each assessment day as a time point.

For each outcome (primary or secondary) and each moment mean, median, range, and stability envelope will be calculated. The level of change and difference between the first and last values of each period will be compared. The next step includes the calculation trend using the split middle method of trend estimation. After this procedure, percent of data points within the stability envelope (80% of data points between ±25% of median) will be considered. The final step is using the “freehand method” to evaluate data path [38].

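### Dividing each EMG by its own peak removes any overall amplitude change, so the amplitude indicator of fatigue cannot validly be compared across the shift or between A and B

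*Protocol article*

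**What the plan says.** The Data Collection and Outcomes section makes fatigue a primary outcome: "Fatigue will be assessed by electromyography (EMG) and musculoskeletal symptoms by the Nordic Musculoskeletal Questionnaire".

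The Electromyography section sets out the processing in this order:

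1. Filtering: "a fourth-order Butterworth band-pass filter from 10 to 500 Hz will be applied".
2. Normalisation by a method that "divides each point that constitutes the processed EMG by the peak value acquired from the same EMG".
3. Amplitude: "The root-mean-square of the EMG data and the averaged rectified value will be calculated to determine the signal amplitudes".
4. Interpretation: "Muscle fatigue will be characterized by median frequency and amplitude".

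The Study Procedure section describes the recordings as "measurements for each period of 5 cycles of the performed task", in four periods of the working day. The Data Analysis section says that results will be "compared in-between the different time points of the work shift and longitudinally considering each assessment day as a time point". The article names no reference contraction, fixed reference recording or unnormalised amplitude, and it does not say what counts as one EMG when the peak is taken (a cycle, a five-cycle recording or a day).

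**The concern.** An amplitude sign of fatigue is a change in the size of the signal between recordings. Dividing a recording by its own maximum sets that maximum to 1, whatever the original size. A muscle working at a uniformly higher level late in the shift, or at a uniformly lower level in a feedback phase, then gives the same normalised RMS and ARV as before.

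The study has 5 workers and relies on structured visual analysis, so conclusions come from plotted levels and trends. An amplitude trace that stays flat because of the normalisation could be read as no fatigue or no benefit. It could also seem to contradict a real shift in median frequency.

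**Working it through.** The plan states no figure for this point, so there is nothing of its own to reproduce. The cancellation is algebraic. The simulations only illustrate it.

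**Inputs from the protocol (Electromyography):** 2000 Hz sampling, fourth-order Butterworth 10 to 500 Hz, own-peak division, then RMS and ARV.

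**Assumptions:** 60 s burst-type signals with five bursts, and the gains, burst shapes and spectra given below. None of these is in the protocol.

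**1. Algebra.** For a recording x and the same recording multiplied by k > 0:

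RMS(kx)/max|kx| = k·RMS(x) / (k·max|x|) = RMS(x)/max|x|

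The same holds with ARV in place of RMS. The remaining quantity, RMS/peak, is an inverse crest factor.

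**2. Same signal, gain only.**

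| True gain | Raw RMS | Own-peak RMS | Own-peak ARV |
|---|---|---|---|
| 1.0 | 0.513 | 0.110 | 0.065 |
| 1.2 | 0.616 | 0.110 | 0.065 |
| 1.5 | 0.770 | 0.110 | 0.065 |
| 2.0 | 1.027 | 0.110 | 0.065 |

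**3. Independent early and late recordings, 60 pairs per gain.** For true gains of 1.2, 1.5 and 2.0, the mean late/early ratio of raw RMS was 1.20, 1.50 and 2.00. The own-peak ratio was 1.02 each time, whatever the true gain.

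**4. Fatigue-like change (gain 1.3 with a lower spectrum).** The raw RMS ratio was 1.30 and the own-peak RMS ratio 1.00. The median frequency ratio was 0.80 with or without normalisation, because scaling a signal does not move its spectrum.

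**5. Change of shape (tonic level between bursts raised from 0.15 to 0.50).** Raw RMS went from 0.512 to 0.807 (0.807/0.512 = 1.58, or +58%). Own-peak RMS went from 0.119 to 0.141 (0.141/0.119 = 1.18, or +18%). The index can therefore move, but not in proportion to amplitude.

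**6. Alternative reading: one peak per day.** Four windows with true gains 1.00, 1.10, 1.05 and 1.30 gave normalised ratios to the first window of 1.00, 1.10, 1.05 and 1.29, the same as raw. A second day with every window multiplied by 0.80 gave raw B/A ratios of about 0.80 and normalised ratios of about 0.99. The within-shift contrast survives and the uniform day-level contrast does not.

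**7. First-window reference.** Let r_j = RMS_j/RMS_1 for window j of a day. Any change from the first window to window j is kept. A factor c common to the whole day cancels, since c·RMS_j/(c·RMS_1) = r_j. For the day multiplied by 0.80, the gains 0.80, 0.88, 0.84 and 1.04 give 1.00, 1.10, 1.05 and 1.30, the same profile as the unscaled day. This reference serves the within-shift comparison only.

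**The case against.** Four fair points can be made in favour of the plan.

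- **The unit is undefined.** If one peak serves a whole day, the across-shift comparison survives (step 6). This stands as a limit, and the loss across the shift depends on the per-recording reading. That reading is the natural one, and the day-level contrast fails on either.
- **The text does not say outright that RMS and ARV use the normalised signal.** That is true, but the order of the sentences points that way. Normalisation also cannot affect median frequency, so amplitude is the only named fatigue indicator on which it could act.
- **The index is not blind.** It responds to burst shape (step 5). This stands, but such a movement is not a measure of amplitude level and could mislead if plotted as one.
- **Within-shift comparison is already planned** in the Data Analysis section. This stands: the fault lies in the quantity compared, not in a lack of within-shift comparison.

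A reader might infer more: that the amplitude result will be null or random whatever the truth, or that the trial could find no benefit purely because of this step. The documents do not support that. Exact cancellation applies to an overall gain only, median frequency remains a working indicator of the same primary outcome, and the Nordic questionnaire is a separate primary outcome. Nor should the extra noise from relying on a single maximum sample be given as a trial figure, since its size depends on the simulated signal. Electrode re-application between assessment days is likely, as the electrodes are disposable and the phases last 4 weeks, but it is inferred and not stated.

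**Conclusion.** The point holds as a fault in a stated rule. It is not a matter of detail left to another document. With one peak per recording, the whole of any overall amplitude change is removed, and normalised RMS and ARV become a signal-shape index that cannot validly be compared across the shift or between A and B. With one peak per day, the loss is confined to uniform day-level differences between A and B. One of the two EMG indicators of a primary outcome is compromised and the other is intact.

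The cancellation needs no assumption beyond the order of processing and the unit of the peak. The simulated values in steps 2 to 6 rest on assumed signals and only illustrate it.

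**What to change.** In the Electromyography section, replace own-peak division with one common reference per worker, muscle and day, and state that unit. An example is the RMS of that day's first window, with the electrodes kept in place through the shift. State that RMS and ARV are computed against this reference. In the Data Analysis section, make the daily amplitude value the within-shift change (later windows relative to the first), plot it alongside the within-shift change in median frequency, and compare both across A1, B1, A2 and B2.

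State the downside in the text: this reference does not recover an intervention effect already present in the first window of the day, so day-level amplitude differences between A and B should not be interpreted from it. If that contrast is wanted, it needs a reference that does not come from the compared recordings, such as a standard reference contraction each day, which would be an added procedure.

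The basic change needs no new recordings and no maximal contraction. It costs a revised normalisation step in the MATLAB script, short edits to two sections, a different plotted quantity, and the practical burden of keeping electrodes on for a full factory shift. A day without a usable first window would have no amplitude value. Settle this before the first assessment, because the electrode requirement cannot be met afterwards.
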